**Colorectal-Anal distress Inventory 8 (CRAD-8)**

|  | ***Do You…*** |  |  |  |  |  |
| --- | --- | --- | --- | --- | --- | --- |
|  | Feel you need to strain too hard to have a bowel movement? |  |  |  |  |  |
|  | Feel you have not completely emptied your bowels at the end of a bowel movement? |  |  |  |  |  |
|  | Usually lose stool beyond your control if your stool is well-formed? |  |  |  |  |  |
|  | Usually lose stool beyond your control if your stool is loose? |  |  |  |  |  |
|  | Usually lose gas from the rectum beyond your control? |  |  |  |  |  |
|  | Usually have pain when you pass your stool? |  |  |  |  |  |
|  | Experience a strong sense of urgency and have to rush to the bathroom to have a bowel movement? |  |  |  |  |  |
|  | Does part of your bowel ever pass through the rectum and bulge outside during or after a bowel movement? |  |  |  |  |  |

**Urinary distress Inventory 6 (UDI-6)**

|  | ***Do You…*** |  |  |  |  |  |
| --- | --- | --- | --- | --- | --- | --- |
|  | Usually experience frequent urination? |  |  |  |  |  |
|  | Usually experience urine leakage associated with a feeling of urgency, that is, a strong sensation of needing to go to the bathroom? |  |  |  |  |  |
|  | Usually experience urine leakage related to coughing, sneezing, or laughing? |  |  |  |  |  |
|  | Usually experience small amounts of urine leakage (that is, drops)? |  |  |  |  |  |
|  | Usually experience difficulty emptying your bladder? |  |  |  |  |  |
|  | Usually experience pain or discomfort in the lower abdomen or genital region? |  |  |  |  |  |

**Part-VII: The International Consultation on Incontinence Questionnaire**

**Instructions:**

Many people leak urine some of the time. This study is aimed to find out how many people leak urine and how much this bothers them. Please answer the following question, thinking about how you have been, on average, in the last four weeks.

| S.No | Questions | Responses |
| --- | --- | --- |
|  | How often do you leak urine? | 1. = never 2. = once a week 3. = 2-3 times a week 4. = once a day 5. = several times a day 6. = all the time |
|  | How much urine do you usually leak? | 0= none  2 = a small amount  4 = a moderate amount  6 = a large amount |
|  | Overall, how much does leaking urine interfere with your everyday life? (give a value between 0 (not at all) and 10 (a great deal) | 0 1 2 3 4 5 6 7 8 9 10 (encircle the appropriate number) |
|  | When does urine leak? Select all that apply to you | 0 = never leak  1 = before getting to the toilet  2 = leaks when coughing or sneezing  3 = leaks when sleeping  4 = leaks when exercising  5 = leaks when finished urinating and dressing  6 = leaks for no reason  7 = leaks all the time |

**Part VIII: Obstetric Fistula Screening Tool**

| Sr. No | Questions | Responses |
| --- | --- | --- |
|  | Have you ever given birth vaginally? | 0 = No 1= YES |
|  | Have you faced labor that lasted more than one day and night? | 0 =No 1= Yes |
|  | Do you have continuous leakage of urine? | 0 =No 1 =Yes |

**Part-IX: Pelvic Organ Prolapse Quantification (POP-Q)** (to be used by pelvic examiners)

**Instructions**: Measure the descent of all the nine measurement points in the POP-Q system. Measure all points at a maximum Valsalva, except Total Vaginal Length (TVL) which is measured at rest. Record measurements in centimeters to the nearest 0.5cm. TVL= is measured from Hymenal remnant to point D, Aa is an arbitrary fixed point on the anterior vaginal wall, which is 3cm back from the middle of the external urethral meatus in normal cases. Point Ba is the lowest part of the upper anterior vagina. This point is not a fixed point like Aa. It can be anywhere along the vaginal wall above the first 3cm (Aa). Point Ap and Bp are similar points to Aa and Ba but found on the posterior vaginal wall. GH is measured from external urethral meatus to hymenal remnant, PB from the hymenal remnant to the anal opening, C is the lowest part of cervix and point D is the insertion of uterosacral ligaments to the cervix. Both points are measured relative to the plane of hymenal remnants.

Height: ____________________ cm

Weight: ____________________ kg

Abdominal Striae: ­­­­­­­­­­­­­­ □ yes □ No

**POP-Q:**

| Aa = | Ba = | C = |
| --- | --- | --- |
| Gh = | Pb = | TVL = |
| Ap = | Bp = | D = |

...

Circumference of prolapse (cm): __________________________

Standing Cough Stress Test: □ positive □ negative Volume (mL):______

**PART-X: PROLAPSE RELATED QUALITY OF LIFE (FOR CONFIRMED POP-PATIENTS ONLY**)

**Instruction**: Below are some daily activities affected by prolapse. Please tell me how much your prolapse problem affected you (tick the correct column).

| **Domain** | **Items** | **0 Very good** | **1 Good** | **2 Fair** | **3 Poor** | **4 Very poor** |
| --- | --- | --- | --- | --- | --- | --- |
| Present general health (GHP | How do you describe your health at present |  |  |  |  |  |
|  |  | **0 Not at all** | **1 Slightly** | **2 Moderately** | **3 A lot** |  |
|  | Prolapse impact on life (PI) |  |  |  |  |  |
| Role limitations | To what extent does your prolapse affect your household task? |  |  |  |  |  |
|  | Does your prolapse affect your job/daily activity outside the home? |  |  |  |  |  |
| Physical/social limitations | Does your prolapse affect your physical activities? |  |  |  |  |  |
|  | Does your prolapse affect your ability to travel? |  |  |  |  |  |
|  | Does your prolapse affect your social life? |  |  |  |  |  |
|  | Does your prolapse affect your ability to see/visit friends? |  |  |  |  |  |
| Personal relationship | Does your prolapse affect your relationship with your partner? |  |  |  |  |  |
|  | Does your prolapse affect your sex life? |  |  |  |  |  |
|  | Does your prolapse affect your family life? |  |  |  |  |  |
| Emotions | Does your prolapse make you feel depressed? |  |  |  |  |  |
|  | Does your prolapse make you nervous/anxious? |  |  |  |  |  |
|  | Does your prolapse make you feel bad about yourself? |  |  |  |  |  |
| Sleep/Energy | Does your prolapse affect your sleep? |  |  |  |  |  |
|  | Does your prolapse make you tired? |  |  |  |  |  |
| Actions taken | Use pad to protect prolapse |  |  |  |  |  |
|  | Do you push up the prolapse |  |  |  |  |  |
| Severity measures | Pain/discomfort due to the prolapse? |  |  |  |  |  |
|  | Does the prolapse Prevent you from standing? |  |  |  |  |  |
| **Patient Global Impression of Improvement**  Ask the following questions only for end-line assessment (after intervention). Both the control and interventional group participants will be asked at the end of six months | | | | | | |
| Patient Global Impression of Change | How do you feel about your health after this intervention? | 1= Very much improved  2= Much improved  3= Minimally improved  4 = No change  5= Minimally worse  6= Much worse  7= Very much worse | | | | |

Thank you for your participation

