## Data Collection Tools and Procedures

Data about health-related quality of life among patients with POP will be measured using the disease-specific tool called Prolapse-Quality of Life (P-QoL) (33). It was initially developed in 2005 to measure the severity of prolapse symptoms, its impact on patients’ health-related quality of life, and treatment outcome among English-speaking women. It is prolapse specific, a multidimensional tool with nine domains and 20 items. The domains include general health perception (GHP), prolapse impact (PI), role (RL), physical limitation (PL), social limitation (SL), personal relationship (PR), emotional disturbance (EMO), sleep/energy disturbance (SE), and severity measures (SM). Each domain has its own items/questionnaire each containing four points (0= none/not at all, 1= slightly or little, 2= moderately, and 3= a lot). Each domain has a score of 0 to 100, a higher score indicating poor quality of life. This tool was translated to and validated in the Amharic version. The Amharic version had categorized the nine domains into three major components. These components include Physical (physical component/PC; which is composed of general health perception, prolapse impact, physical limitation, social limitation, role, and severity measure), psychological, which includes: emotional disturbance and sleep disturbance) and personal relationship (25). In the current study, the Amharic version will be used after being translated into Sidaamu Afoo and translated back to check for consistency.

In addition, after the intervention, to evaluate patients' overall satisfaction with their post-intervention conditions, Patient Global Impression-Index (PGI-I) tool (27, 34) will be used. This tool measures how patients perceive their improvement after intervention. It contains a single item of a seven-point scale (7=very much worse, 6=much worse, 5=minimally worse, 4 = no change, 3=minimally improved, 2=much improved, and 1=very much improved). This score will be re-categorized as disease deterioration (minimally worse, much worse, or very much worse), no change (the same, remain stable), and disease improved (very much improved, improved, or minimally improved). This tool will be used after translated into the local language (Sidaamu Afoo) and back to English to check for consistency.

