## Data Measurements

Study participants’ adherence to training protocol will be evaluated at each follow-up time (week 2, 6, 10, and 15). At week two, women will be assessed for adherence to pelvic floor muscle exercise in the last two weeks (a few days per week, once per week, a few times a week, once a day, three times a day). At weeks six, 10, and 15, they will be assessed for adherence to pelvic floor muscle exercise in the last four weeks using similar questions used on week two (a few days per week, once per week, a few times a week, once a day, three times a day). In addition, they will be assessed for improvement in prolapse quality of life at 10 and 15 weeks. At the end of six months, the overall adherence to training protocol will be evaluated from their dairy or report of pelvic muscle trainer. Women’s adherence to training protocol is considered adequate when they complete at least 80% of the training sessions (24).

Prolapse quality of life will be measured for each three components of the tool separately. Each component will have a score of zero (0) to 100. The mean change of each component will be evaluated at the end of six months for both arms. The mean change will be compared between the two groups (intervention and control groups) to measure the effect of Pelvic Muscle Training. The secondary outcome, women’s perceived improvement after the intervention will be measured as improved, the same, or worsened based on Patient Global Impression of Improvement (PGI-I).

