**Woreda_________ kebele________ Enumeration Area____________ Code_____ Mobile______________________**

| **Sr. No.** | **Questions** | **Response category** | **Skip to** |
| --- | --- | --- | --- |
|  | What is your current Age? | __________years completed |  |
|  | Where is your permanent place of residence? | 1. Urban 2. Rural |  |
|  | What is your current marital status? | 1. Never married 2. Married 3. Widowed 4. Divorced 5. Separated |  |
|  | What is your Religion? | 1. Ethiopian Orthodox 2. Protestant 3. Muslim 4. Catholic 5. Adventist 6. Other(specify)____________ |  |
|  | What is your main Occupation? | 1. Housewife 2. Farmer 3. Government employee 4. Nongovernmental employee 5. Private Business 6. Student 7. Others Specify)____________ |  |
|  | What is your Ethnicity? | 1. Sidama 2. Wolayta 3. Amhara 4. Gurage 5. Oromo 6. Other(specify)___________ |  |
|  | What is your level of education? | 1. Unable to read and write 2. Able to read and write without formal education 3. Primary Education 4. Secondary Education 5. Above secondary |  |
|  | What is your Husbands’ level of education?  Ask only if she is married (refer back to Q-103). | 1. Unable to read and write 2. Able to read and write without formal education 3. Primary Education 4. Secondary Education 5. Above secondary |  |
| **Part-II: Lifestyle Questions**  Ask the following questions one at a time and write the response on the space provided or encircle the appropriate response from the options listed. | | | |
|  | On average, for how long do you carry heavy objects/day (water, big baby, wood, stone, cereal, or grain) | -------- hrs |  |
|  | Have you ever smoked cigarettes? | 1. No 2. Yes |  |
|  | Do you have a family member who had Pelvic organ prolapse? | 1. No 2. Yes |  |
|  | Did you ever have a chronic cough (>3weeks) | 1. No 2. Yes |  |
|  | Did you ever have constipation (difficulty of defecation? | 1. No 2. Yes |  |
|  | Did you ever have a confirmed diabetes mellitus? | 1. No 2. Yes |  |

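### The personal relationship outcome is not validly measured for women without a partner: the form has no 'not applicable' answer, and the plan has no rule for them

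*Protocol*

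**What the plan says.** **Instrument.** Paper-IV, Data Collection Tools and Procedures, describes the P-QoL: "It is prolapse specific, a multidimensional tool with nine domains and 20 items". The answers are described as "each containing four points (0= none/not at all, 1= slightly or little, 2= moderately, and 3= a lot", and the scale as follows: "Each domain has a score of 0 to 100, a higher score indicating poor quality of life". Paper-II describes the tool in the same terms.

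**Components.** Paper-IV groups the nine domains into three components. The physical one is "composed of general health perception, prolapse impact, physical limitation, social limitation, role, and severity measure". The psychological one holds emotional and sleep disturbance. Personal relationship stands alone. Under Data Measurements: "Each component will have a score of zero (0) to 100". The analysis sections of Papers III and IV count these three and POP-SS as the four outcomes, each tested at P < 0.0125.

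**Form.** In Annex II, Part X, the personal relationship items are "Does your prolapse affect your relationship with your partner", one on sex life and one on family life. All have columns 0 to 3 and no column for a question that does not apply. The Sidaamu Afoo form in Annex III has no such column either.

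**Population.** The marital status item in Annex II, Part One offers "1. Never married 2. Married 3. Widowed 4. Divorced 5. Separated". The Paper-II survey, which supplies the trial's participants, excludes women who have never had intercourse. Neither it nor the Paper-III eligibility criteria require a partner.

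**Missing data.** Paper-II plans multiple imputation for any missing data. Paper-III adopts its missing-data handling, and Paper-IV follows Paper-III.

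**The concern.** Two of the three items behind a tested outcome presuppose a partner or a sex life. For a woman with neither, the form allows no truthful answer, and the protocol does not say what to enter.

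The problem arises when the data are recorded. Once a 0 has been ticked, nobody can tell whether it meant no impact or no partner. Baseline marital status helps only in part, because unmarried is not the same as unpartnered. Adjusting for it, as the Paper-IV covariate list allows, does not restore the missing distinction. The P-QoL will not be validated in Sidaamu Afoo (Paper-IV, Quality Assurance), so no planned psychometric step would show the problem.

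At stake are an understated baseline and a diluted treatment effect if zeros are entered, or partly invented data if blanks are imputed.

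**Working it through.** **1. Status of the outcome.** Four outcomes share 0.05, and 0.05/4 = 0.0125. The plan's threshold is reproduced, and personal relationship is one of the four.

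**2. Can the situation arise?** The survey exclusion removes only women who have never had intercourse. Widowed, divorced and separated women pass both sets of criteria, and the form lists them. Elsewhere the form does use a condition: the question on the husband's education is put only to married women. Part X has no equivalent for the partner and sex-life items.

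**3. Consequence if 0 is ticked.**
- Full range of the component: 3 items x 3 points = 9 raw points, so the score is 100 x raw/9.
- With partner and sex life at 0, only family life can vary. The maximum is 100 x 3/9 = 33.
- Let d be the mean change per item where the item applies, equal across items, and s the share of unpartnered women, equal in both arms. A partnered woman changes by 100 x 3d/9. An unpartnered woman coded 0 at both visits changes by 100 x d/9.
- Overall mean change: (1 - s) x 100 x 3d/9 + s x 100 x d/9 = (100 x 3d/9) x (1 - 2s/3).
- The proportional loss is therefore 2s/3, and the difference between arms shrinks by the same factor.

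| Assumed s | Loss 2s/3 |
| --- | --- |
| 10% | 7% |
| 20% | 13% |
| 30% | 20% |

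The protocol gives no value for s.

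**4. Consequence if the item is left blank.** The blank falls under multiple imputation. The model would fill in how much prolapse affects a partnership that does not exist. That value is not missing; it is undefined.

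**5. Items and ranges on the form.** By form label: general health 1, prolapse impact 1, role 2, physical/social 4, personal relationship 3, emotions 3, sleep/energy 2, actions taken 2, severity 2.
- Sum: 1 + 1 + 2 + 4 + 3 + 3 + 2 + 2 + 2 = 20, the stated total. Without the two 'Actions taken' items ("Use pad to protect prolapse" and pushing up the prolapse) it is 18.
- The Paper-IV text reaches nine domains by separating physical from social limitation and names no actions domain. The form merges those two and adds one. The component of the two action items is therefore unstated.
- The general health item has five columns, 0 to 4, against the four points in the text.
- Psychological component: 5 items x 3 = 15 raw points, all within the 0 to 3 rule. It reaches 0 to 100 without difficulty.

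**6. Does the assignment of the action items matter?** Scale each item by its own range and average. A woman scores 1 on each of the ten physical items and 3 on both action items.
- Without the action items: (1/4 + 9 x 1/3)/10 = 3.25/10 = 32.5.
- With them: (3.25 + 2)/12 = 5.25/12 = 43.8.

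The choice changes the score, so it must be fixed in advance.

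**The case against.** **Nothing tells the interviewer to tick 0.** This is correct. Part X only asks for the right column to be marked, and a blank is equally possible. A reader might infer that zero coding is required; the documents do not support that. The 33-point cap and the dilution hold only if zeros are entered. The blank route leads to imputation, however, so neither route gives a valid score.

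**Marital status is not partnership.** This also stands. A separated or divorced woman may truthfully answer that prolapse has affected her relationship a lot, and the protocol's own background links disclosure of prolapse to divorce. This is a reason to let the woman say whether the item applies rather than derive it from marital status.

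**Scoring detail may sit in a statistical analysis plan.** That is fair for formulas. A reader might infer that the physical component can exceed 100, because dividing the general health item by 3 gives 4/3 = 133 for that domain, and 31/30 = 103 for ten pooled items. No section prescribes that division; dividing by the item's own range keeps 0 to 100. What remains is a mismatch between text and form. A later analysis plan cannot, however, recover an answer option that was never offered.

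**The action items are part of the tool.** The total of 20 is reached only by counting them, so they may be meant for one of the named domains. A reader might infer that they lie outside every component. The documents show only that their domain is not stated.

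**Translation.** As read, the first and third personal relationship items in Annex III are worded almost identically. If the first in fact asks about family, only the sex-life item is inapplicable: the cap becomes 6/9 = 67 and the loss s/3. A fluent speaker should check this.

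**Conclusion.** The concern holds for one of the four tested outcomes. Personal relationship has no valid score for women without a partner, and the plan leads either to a false 'no impact' or to an imputed answer about a partner who does not exist.

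The size depends on an unpartnered share that the protocol does not give. If zeros are entered, all items respond alike and the share is equal in both arms, the effect is diluted by 7% to 20% for shares of 10% to 30%. Paper-IV makes no power claim for the P-QoL, so no stated power is contradicted.

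The 0 to 4 general health item and the two unassigned items are secondary mismatches affecting the physical component. A reader might conclude that the form cannot produce any of the three 0 to 100 components. That goes too far: the psychological component is intact, the physical one needs only a stated rule, and personal relationship works for women with a partner. This is a cheap improvement worth making, not a failure of the trial.

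**What to change.** **Main change, before baseline interviews.**
- In Part X of Annex II and Annex III, add a 'not applicable' answer to the partner and sex-life items, and check the Sidaamu Afoo wording of the partner item.
- In Paper-IV, Data Measurements, score personal relationship as the mean of the applicable items rescaled to 0 to 100.
- State that items marked not applicable are not imputed.
- Repeat the analysis in partnered women as a sensitivity analysis.

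**To reconcile in the Paper-II and Paper-IV text.**
- State that the general health item runs 0 to 4 and that each item is scaled by its own range.
- State which domain and component the two 'Actions taken' items enter, or that they are not scored.

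**Cost.** One extra tick box on two items and a few sentences on scoring. The downsides are that some women's personal relationship score will rest on one item, and that the form departs slightly from the translated instrument. The analysis in partnered women keeps a comparison on the full three-item score.

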## Data Measurements

At each visit, women's adherence to pelvic floor muscle training will be evaluated by their pelvic muscle trainer. At week two, women will be assessed for adherence to pelvic floor muscle exercise in the last two weeks (three times a day, once a day, a more than once per week, once per week, a more than one days per week). At weeks six, 10, and 15, they will be assessed for adherence to pelvic floor muscle exercise in the last four weeks using similar questions used on week two (three times a day, once a day, a more than once per week, once per week, a more than one day per week). In addition, they will be assessed for prolapse symptoms at weeks 10 and 15.

At the end of six months, the overall adherence to training protocol will be evaluated from their dairy or report of pelvic muscle trainer. Women’s adherence to training protocol is considered adequate when they complete at least 80% of the training sessions (24). This will be calculated at each visit based on the training session and finally compiled.

The primary outcome of the study is a change in prolapse symptoms measured by POP-SS. The POP-SS is the same measurement with study one which measures the frequency of prolapse symptoms in the last four weeks, measured by seven items with a Likert-scale of 0 to 4 scale (0= never felt symptom, 1= occasionally, 2= sometimes, 3= most of the time and 4= all of the time). The total score will be calculated by summing up all responses for the seven-question and the total score will range from 0 to 28, the highest value indicating the severity of prolapse symptoms (25, 26). At the end of the six months, the mean change in prolapse symptoms from the initial visit will be compared between the two groups (intervention and control groups) to measure the effect of pelvic muscle training.

The secondary outcome, women’s perceived change in prolapse symptom since the start of the intervention, will be measured as improved, the same, or worsened based on Patient Global Impression of Change (PGIC) (14, 27).

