## Data Collection Tools and Procedure

The Pelvic Organ Prolapse symptoms will be assessed using a translated and validated Sidaamu Afoo version of the POP-SS questionnaire. This tool will be obtained from Paper I of this dissertation project (Paper I). After the intervention, in addition to the POP-SS tool, the Patient Global Impression of Change (PGIC) tool will be used to evaluate patients’ perceived change in prolapse symptoms. The PGIC evaluates overall health status as perceived by the patient in a seven-point single item scale measured as 1= very much improved, 2= much improved, 3= minimally improved, 4 = no change, 5= minimally worse, 6= much worse or 7= very much worse. This scale can be classified into three major categories for description purposes: worsen or disease deterioration (very much worse, much worse, or minimally worse), the same (no change), and improved (minimally improved, much improved, and very much improved) (27). The PGIC will be translated into Sidaamu Afoo by native speakers and translated back to English to check its consistency.

After six months of intervention, the same data collectors of the baseline data will go to the house of the study participants and collect the data through face-to-face interviews. These data collectors are those who were recruited by Hawassa University to collect data from the HDSS site and fluent in Sidaamu Afoo.

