## Variables

The primary outcome variable of this study is a change in Health-Related Quality of Life (HRQL). The secondary outcome is participants’ perceived change in Prolapse impact on their quality of life measured by Patient Global Impression of Improvement (PGI-I) (34). The intervention is Pelvic Floor Muscle Training and other covariates include degree of POP, the severity of POP-SS, adherence to Pelvic Floor Muscle Training protocol, maternal age, location of POP (anterior, posterior or apical), number of childbirth, level of education, history of depression, need for fertility, body mass index, trauma, marital status, occupation, age at first delivery, place of delivery, history of prolonged labor, medical problem (chronic cough, diabetes mellitus), family history of POP, mode of delivery.

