**PART-V: POP-SS**

**Direction**

The following seven questionnaires are standard tools used to measure prolapse symptoms. Each item/question has 0 to 4 possible response scales. Inform the participant how to give a rate for each item based on how often she felt the prolapse symptom in the last four weeks (Put ‘X’ in the right box under each response scale).

Dear participant, please tell me how often did you feel the following POP symptoms in the last four weeks? (Please give the rating scale as follows: 0= never felt symptom in the last four weeks, 1= occasionally, 2= sometimes, 3= most of the time and 4= all of the time)

| **S.no** | **POP-Symptoms** | **0**  never felt symptom in the last four weeks | **1**  occasionally | **2**  sometimes | | **3**  most of the time | **4**  all of the time |
| --- | --- | --- | --- | --- | --- | --- | --- |
|  | A feeling of something coming down from or in your vagina? |  |  |  | |  |  |
|  | An uncomfortable feeling or pain in your vagina which is worse when standing? |  |  |  | |  |  |
|  | A heaviness or dragging feeling in your lower abdomen/tummy? |  |  |  | |  |  |
|  | A heaviness or dragging feeling in your lower back? |  |  |  | |  |  |
|  | A need to strain (push) to empty your bladder? |  |  |  | |  |  |
|  | A feeling that your bladder has not emptied completely? |  |  |  | |  |  |
|  | A feeling that your bowel has not emptied completely? |  |  |  | |  |  |
|  | Which of the symptoms above (questions 1–7) causes you most bother? | ……………. | | | | | |
|  | For how long have you felt one of the most chronic symptoms? | ……… | | | | | |
| **Patient Global Impression of Change questionnaire**  Ask the following questions only at end-line assessment (after intervention). Both the control and interventional group participants will be asked at the end of six months. | | | | | | | |
|  | How do you Perceive the change in prolapse since the start of the intervention? | | | | 1= Very much improved  2= Much improved  3= Minimally improved  4 = No change  5= Minimally worse  6= Much worse  7= Very much worse | | |

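### Paper IV's PGI-I secondary outcome is not what the form asks: the English item is about health in general, and the Sidaamu Afoo row repeats the urine-leakage timing question

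*Protocol*

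**What the plan says.** Paper IV describes its secondary outcome in three places and prints it on two forms.

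- Paper IV, Variables, gives the outcome as "perceived change in Prolapse impact on their quality of life measured by Patient Global Impression of Improvement (PGI-I").
- Paper IV, Data Measurements, shortens this to "perceived improvement after the intervention will be measured as improved, the same, or worsened", with no object named.
- Paper IV, Data Collection Tools and Procedures, says the tool evaluates "overall satisfaction with their post-intervention conditions, Patient Global Impression-Index (PGI-I) tool". It then adds that the tool captures how patients see their improvement, and lists seven answers to be collapsed into three.
- Annex II (English), Part X, final row: "How do you feel about your health after this intervention", with seven answers from very much improved to very much worse. The block heading says Improvement; the row label says Change.
- Annex III (Sidaamu Afoo), Part X, final row: the same sentence as the fourth item of Part VII of that annex, paired with the seven improvement and worsening answers.

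Paper III has its own global item, the PGIC. Its Data Measurements section defines the outcome as "perceived change in prolapse symptom since the start of the intervention", and the form in Annex II Part V asks "How do you Perceive the change in prolapse since the start of the intervention".

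**The concern.** A secondary outcome is only as good as the question that produces it. The answer to this row decides which women Paper IV reports as improved, unchanged or worse. If the row asks about health in general, those categories describe something other than the outcome the protocol defines. If it asks when urine leaks, they describe nothing interpretable, because the printed answers do not fit the question. Analysis cannot repair either case, since the needed answer was never collected. The outcome definition and the annexed form are both part of the protocol, so this is not a detail left to a statistical analysis plan.

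**Working it through.** No arithmetic is needed to establish the mismatch; the check is a comparison of texts.

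1. **Outcome against English item.** The outcome has three elements: change, prolapse, and impact on quality of life. The English item, "How do you feel about your health after this intervention", contains neither of the last two. Change enters only through the answer options.

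2. **Does the protocol treat general health and prolapse impact as the same thing?** No. Paper IV lists general health perception and prolapse impact as separate P-QoL domains. Annex II Part X gives them separate rows with different scales: present health is rated 0 to 4 from very good to very poor, and prolapse impact 0 to 3 from not at all to a lot.

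3. **Labels.** The same tool is called Improvement (Paper IV, Variables and Data Measurements, and the Part X block heading), Index (Paper IV, Data Collection Tools and Procedures) and Change (the row itself). Change is the name of Paper III's instrument.

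4. **Sidaamu Afoo form.** The Ethical Considerations section says data will be collected in Sidaamu Afoo. The sentence in the final row of Annex III Part X is identical, including its bracketed instruction, to the fourth item of Annex III Part VII. The fourth item of the English Part VII asks when urine leaks. This reading rests on the identical sentence and its position in the incontinence section, not on an independent translation.

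5. **Would the planned safeguard catch it?** Paper IV plans translation of the PGI-I and back-translation to English. Comparing the back-translation with the English text should expose the Sidaamu Afoo row. It cannot expose the English item, because a faithful translation of that item would pass. Repairing the Sidaamu Afoo row from the present English text would therefore replace a question on leakage with one on general health.

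6. **What else is touched?** Paper III, Data Management and Analysis, counts four outcomes for the correction: the POP-SS change and three P-QoL components. That gives 0.05 / 4 = 0.0125. Neither global-impression item is among them. The sample size is derived from POP-SS in Paper III and carried over to Paper IV. None of this changes.

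**The case against.** The strongest reply is context. The English row closes a section headed as prolapse-related quality of life for confirmed patients. The section's instruction asks how the prolapse affected the woman, most earlier items name the prolapse, and the question is tied to the intervention. Some women would answer with their prolapse in mind. That stands as mitigation, but it leaves the meaning of each answer uncertain. The section also opens with a plain question on present health, so a second question about health can reasonably be heard the same way.

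It can also be said that Paper IV's descriptions are closer than they look: the tool description goes on to speak of perceived improvement, which fits Data Measurements. That is fair. The decisive conflict is between the outcome in Variables and the forms.

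Three stronger readings are tempting, and the documents do not support them.

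- A reader might infer that Paper III's global outcome is mis-measured too, because its tool section says "The PGIC evaluates overall health status as perceived by the patient in a seven-point single item scale". The sentence just before that one says the tool is for perceived change in prolapse symptoms, and the outcome text and the English form item also refer to prolapse. The English item would collect the intended kind of answer; this is a wording point.
- A reader might want to state how much of the treatment effect is lost. The documents give no correlation between change in general health and change in prolapse impact. Under a simple proxy model the proportion lost is 1 − r: 70%, 50% or 30% at assumed values of 0.3, 0.5 or 0.7. Those figures only restate the assumption. The model is also linear, while the outcome is reported in three categories, and it does not apply to the Sidaamu Afoo row at all.
- A reader might infer that Paper IV could not reach its conclusion on prolapse-related quality of life. That conclusion rests on the primary outcome, the change in the three P-QoL components, which this row does not feed.

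**Conclusion.** The point holds for one secondary outcome. On the English form the PGI-I row asks about a different construct from the one Paper IV defines. On the Sidaamu Afoo form as printed it repeats the leakage-timing item. Used unchanged, the forms would leave perceived change in prolapse impact on quality of life unmeasured for every woman interviewed at end-line, in both arms. The separate PGIC item would still give a prolapse-specific rating of change, but not of impact on quality of life.

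The primary outcomes, the significance level and the sample size are unaffected, and no size of dilution can be derived. The conclusion assumes that the annexed forms are those to be fielded and that the repeated Sidaamu Afoo sentence means what its English counterpart in Part VII says. If the Sidaamu Afoo row were replaced by a faithful translation of the present English item, the mismatch with the outcome would remain. The correction should be made, though it does not threaten the trial's main comparison.

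**What to change.** Before end-line collection:

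- Make the English PGI-I item in Annex II Part X name the prolapse and its change since the start of the intervention, so that it matches the outcome in Paper IV, Variables. Use the wording of the cited PGI-I instrument where it does this. Keep the seven answers and label the row PGI-I.
- In Paper IV, Data Collection Tools and Procedures, bring the reference to overall satisfaction and the name Index into line with Variables and Data Measurements.
- Replace the final row of Annex III Part X with a translation of the corrected English item, and back-translate it.
- As a minor wording point, change the reference to overall health status in Paper III, Data Collection Tools and Procedure, to agree with Paper III, Data Measurements, and the form in Annex II Part V.

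The cost is one item reworded and re-translated, plus small edits to the protocol text. No question, visit or participant is added.
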